### Sample size

The pilot and feasibility RCT will recruit up to 50 participants or for a maximum of 12 months across three sites. These limits were a condition stipulated by the funder. The nested qualitative study will recruit until data saturation, estimated as up to 25 participants (approximately 16 patients and 9 treating physiotherapists).

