### Assignment of interventions

#### Allocation sequence generation

Patients will be randomised in a 1:1 allocation (in mixed blocks) stratified by site using an online randomisation service provided by the CTU. Mixed blocks are required to reduce the predictability of the randomisation allocations.

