#### Optimised intervention

The optimised physiotherapy treatment package includes patient advice and education, exercise therapy, and provision of a counterforce brace. It will differ from usual care by providing a detailed and consistent approach to treatment based upon best available evidence and omitting treatments lacking evidence of efficacy, such as taping, acupuncture and therapeutic ultrasound. The advice and education component is detailed and supported by high-quality written and videographic materials, developed in consultation with patients. The topics covered not only relate to tennis elbow but also incorporate modifiable lifestyle factors that may improve treatment response and reduce risk of recurrence (Table 1).

**Table 1 Tab1:** The advice and education topics included in the optimised physiotherapy treatment package

Condition-specific advice	General/lifestyle factor advice
What tennis elbow is	Basic pain science
Activity modification	Promotion of self-efficacy
Pacing	General exercise advice
Ergonomics for work or sport	Smoking cessation (if applicable)
Medication advice	Sleep advice
	General diet advice
	Diabetes management (if applicable)

The exercise therapy component consists of a progressive regime incorporating stretching, isometric loading, concentric loading and eccentric loading designed to be adaptable to individual patient’s functional demands. Dosage is clearly defined based upon best evidence, and a novel aspect is that patients will be encouraged to exercise into levels of pain deemed acceptable by the individual patient. Painful exercise has been avoided in the interventions tested in the majority of tennis elbow trials to date, but recent systematic review evidence from the fields of back pain, shoulder pain and heel pain trials suggests it may offer improved short-term pain relief [14].

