### Participant timeline (Table 3)

### Data collection methods

Once consented and prior to randomisation, participants will complete a baseline set of patient-reported outcome measures (PROMs) and demographic data including age, gender, ethnicity, duration of symptoms, occupation, education level, hand dominance and comorbidities. Physical measures of maximum grip strength and pain-free grip strength will be taken by the PI or person delegated to take consent, using an electronic grip strength measuring device (Squegg, https://mysquegg.com/). The Squegg is a US Food and Drug Administration (FDA)-approved dynamometer. Both measures will be repeated three times and a mean value used for analysis.

Patients will be offered the choice of two data collection methods for subsequent follow-up: (1) a paper questionnaire with follow-up questionnaires delivered and returned by post to the CTU or (2) an online system provided by Amplitude Clinical where the questionnaires are completed online using a smartphone, tablet or personal computer with automated follow-up questionnaire links delivered by email and SMS text message.

Patient-reported outcome follow-up data collection will be at 6 weeks, 3 and 6 months using the OPTimisE Follow-up Questionnaire. Patients who do not return the paper questionnaires within 2 weeks will receive reminder telephone calls and emails (according to patient preference) on up to two occasions from the chief investigator. Those who do not respond to the online questionnaires will receive automated reminders by email and SMS text message at 1 week and 2 weeks. The choice of outcome measures includes the core outcome set recently recommended for tennis elbow [21]. See Table 4 below:

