Quantitative data analysis will be descriptive. This feasibility study aims to provide estimates of the consent, intervention fidelity, follow-up and outcome measure completion rates to inform a future main trial. By including 50 participants, we will be able to estimate a consent rate of 25% with a 95% confidence interval of (19%, 31%), an intervention fidelity of 60% with a 95% confidence interval of (46%, 74%) and a follow-up rate and outcome measure completion rate of 70% with a 95% confidence interval of (57%, 83%).Consent rate — measured as a percentage of eligible patients approached to participateIntervention fidelity in the intervention group — measured using CRF data. Fidelity to the intervention will be defined by delivery of at least 6 of the 12 prescribed advice/education topics, evidence of exercise prescription and progression in line with the protocol and provision of an elbow clasp splint. Results will be expressed as a percentage of the patients in the intervention group who received treatment assessed as being faithful to the protocol.Follow-up rate in the intervention group — the actual number of visits (excluding the baseline visit) divided by the maximum number of possible visitsOutcome measure completion rate at 6 months — measured as a percentage of outcome measures completed across both the intervention and usual care groups

If any of the above feasibility outcomes are rated red (do not proceed) as per Table 2, then a future main trial will not be feasible. If any outcomes are rated amber (proceed with changes), but without any red, then a future main trial may be feasible with changes to the protocol. If all outcomes are rated green (proceed), then a main trial is feasible.

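### The follow-up rate covers only the intervention group and counts visits, but its stated precision is that of 50 independent patients; about 25 contribute

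*Protocol article*

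**What the plan says.** Outcomes and Statistical methods in the protocol article both list "Follow-up rate in the intervention group" as a primary feasibility outcome. Statistical methods defines it as "the actual number of visits (excluding the baseline visit) divided by the maximum number of possible" visits. The unit counted is therefore the visit, and the population is one arm.

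The same section gives the precision expected from 50 participants, with one interval shared by two outcomes: "a follow-up rate and outcome measure completion rate of 70% with a 95% confidence interval of (57%, 83"%). The second of these, outcome measure completion at 6 months, is measured across both groups.

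Sample size states: "The pilot and feasibility RCT will recruit up to 50 participants or for a maximum of 12 months across three sites". Allocation sequence generation states: "Patients will be randomised in a 1:1 allocation (in mixed blocks) stratified by site".

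Under Statistical methods, a single red rating on any primary feasibility outcome means that a main trial is not feasible. Table 2 holds the cut-offs and Table 3 the schedule; neither can be read in the text reviewed.

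**The concern.** A precision statement should describe the quantity that will be estimated. Here it carries the sample size of the whole trial, while the outcome is confined to one arm. It also treats the result as one yes/no per patient, while the outcome pools several visits from each patient. A reader who relies on it would expect the rate to be known to within 13 points on a base that the outcome does not have.

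There is a second question about what the ratio measures. Data collection methods places outcome follow-up outside the clinic: "a paper questionnaire with follow-up questionnaires delivered and returned by post to the CTU", or an online system. Grip strength after baseline is reported by patients through the same follow-up questionnaire. The footnote to Table 3 names a research appointment and the first physiotherapy treatment appointment. No research visit after baseline is described, so the visits counted appear to be physiotherapy sessions. The value of the ratio then depends on what the maximum number of possible visits means, which the text shown does not say.

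At stake is how firmly a result with a veto over the main trial can be read.

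**Working it through.** **Inputs.** Planned total 50 (Sample size; Statistical methods). Allocation 1:1, so at most about 25 in the intervention group (Allocation sequence generation). Planning rate 70%, 95% interval (57%, 83%) (Statistical methods). The visits per patient, m, and the within-patient correlation, ρ, are not given in the text shown. Values used for them below are assumptions.

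**1. Reproduce the stated figure.** Wald interval p ± 1.96·√(p(1−p)/n), with p = 0.70 and n = 50:
1.96·√(0.21/50) = 0.127, giving 57.3% to 82.7%. This rounds to the stated (57%, 83%). Wilson (56.2% to 80.9%) and Clopper-Pearson (55.4% to 82.1%) at n = 50 do not match it.

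**2. Check the base used for the other outcomes.**
- Consent: "By including 50 participants, we will be able to estimate a consent rate of 25% with a 95% confidence interval of (19%, 31"%). This reproduces at n = 200 (19.0% to 31.0%), that is 50/0.25 patients approached, and not at n = 50 (13.0% to 37.0%). Here the base was adapted to the outcome.
- Fidelity: 60% (46%, 74%), also intervention group only, reproduces at n = 50 (46.4% to 73.6%). At n = 25 it would be 40.8% to 79.2%. It has the same wrong base as the follow-up rate.

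**3. Correct the base.** With n = 25: 1.96·√(0.21/25) = 0.180, giving 52.0% to 88.0%. This keeps the plan's Wald method. At the same rate and n, Wilson gives about 50% to 84% and Clopper-Pearson about 49% to 87%.

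**4. Allow for visits.** With the same m for all patients, each patient's attendance share lies between 0 and 1, so its variance cannot exceed p(1−p). The interval in step 3 is therefore an upper bound on width, reached when attendance is all-or-none. Otherwise the effective sample size is 25m/(1+(m−1)ρ). For an assumed m = 6:
- ρ = 0: 150 visits, half-width 1.96·√(0.21/150) = 7.3 points (62.7% to 77.3%).
- ρ = 0.5: effective size 42.9 (56.3% to 83.7%).
- ρ = 1: effective size 25, half-width 18.0 points (52.0% to 88.0%).

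**5. When would the stated 13 points be right?** Setting the effective size to 50 gives ρ = (m/2−1)/(m−1): 0.25 for m = 3, 0.33 for m = 4, 0.40 for m = 6, 0.43 for m = 8. The stated width can occur, but only by coincidence of two quantities that the plan does not state.

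**6. If the maximum is a fixed cap.** Assume 25 patients, a cap of 6 and no missed visit. If 10 patients finish by agreement after 3 visits, the rate is (15×6 + 10×3)/150 = 80%. If 15 do, it is (10×6 + 15×3)/150 = 70%, the planning value. These patterns are illustrations, not forecasts.

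**The case against.** The strongest defence of the interval is that clustering does no harm here. With an equal maximum, a patient-level interval is already the conservative one, and with weakly correlated visits even the stated 13 points would be too wide. This stands as far as clustering goes: the visit-based definition alone does not make the stated interval too narrow. It does not rescue the base of 50, which is about twice the number of patients who can contribute.

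A reader might also infer that a patient discharged early is counted as lost to follow-up. The documents do not support that. Discharge is not mentioned. The maximum could mean the visits scheduled or offered to each patient, in which case the problem disappears, and Table 3 or the full protocol may settle it. Even under a fixed cap, unused visits lower the ratio in proportion; the patient is not scored as lost. Nor does the description of the exercise regime as "designed to be adaptable to individual" patients' functional demands show that the number of sessions varies. It concerns the exercises, and the text adds that dosage is clearly defined.

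Finally, retention does not rest on this ratio alone. Questionnaire completion at 6 months is its own primary outcome, completion at 6 weeks and 3 months is secondary, and losses with reasons go into the CONSORT diagram.

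**Conclusion.** The precision stated for the follow-up rate is wrong as written: it belongs to 50 independent patients, and the outcome has about 25. On the plan's own method the conservative half-width is 18 points (52% to 88%) instead of 13. This assumes full recruitment, an even split and an equal maximum per patient. The true width may be smaller, down to about 7 points with 6 independent visits each, so the claim is that the stated interval has the wrong basis, not that it must be too narrow.

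The point about the denominator is conditional. It rests on the visits being physiotherapy sessions, which is a well-supported inference, and on the maximum being a fixed cap, which is not stated. It is tempting to go further and say that quick recovery would push the outcome to amber or red. Without the Table 2 cut-offs that cannot be computed, and it is not claimed here.

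The correction should be made because the outcome can veto the main trial and the change is cheap.

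**What to change.** 1. Give the follow-up rate its own planning interval, on about 25 intervention patients: (52%, 88%) as the conservative case, with a note that it narrows if attendance is not all-or-none within patients. Keep the base of 50 for the completion rate, which covers both groups. Correct the base of the fidelity interval at the same time.
2. Compute the final interval with the patient as the unit, by a ratio estimator or a patient-level bootstrap.
3. State what the visits are and what the maximum is. If they are physiotherapy sessions, use the sessions offered to each patient as denominator, so that a course ended by agreement counts as complete.

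One consequence of item 3 is that denominators become unequal, so the bound in item 1 is then approximate. For example, with 10 patients offered 6 sessions and 15 offered 3 (assumed), the all-or-none effective size is (10×6 + 15×3)²/(10×36 + 15×9) = 11025/495 = 22.3, and the half-width is 1.96·√(0.21/22.3) = 19 points instead of 18.

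The cost is a change of wording, and recording sessions offered and how the course ended when the physiotherapy notes are reviewed for the CRF. No extra patients or visits are needed. The price is a wider and more openly uncertain precision statement.

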The physical measures of maximum grip strength and pain-free grip strength will also be reported by patients using the OPTimisE Follow-up Questionnaire. Patients randomised to the OPTimisE intervention will be given a Squegg device to take home at their initial research visit with an information sheet on how to use it. The OPTimisE Follow-up Questionnaire will prompt the patients to use the Squegg device and document three measures each of maximum grip strength and pain-free grip strength. Patients in the usual physiotherapy group will be sent a Squegg device at 6 months. As the device can be used for grip strength training and is not provided as part of usual physiotherapy care, it will only be used at the 6-month time-point for patients in the usual physiotherapy group, to avoid intervention contamination.

Fidelity of the optimised physiotherapy intervention will be measured retrospectively by reviewing the CRF data to establish whether the treatments provided matched the pre-defined protocol. Fidelity will be calculated as a percentage based upon the number of applicable treatment items delivered. Any additional interventions will be noted and discussed in the final data analysis and report. Similarly, CRF data will be used to review the treatment of patients receiving usual physiotherapy to assess for key differences and similarities between the interventions and determine whether there is contamination between the interventions. Adherence to treatment will be measured in both treatment arms using a patient-reported exercise diary that is reviewed by the treating physiotherapist at each session and returned to the chief investigator by the patient after 3 months, via a stamped addressed envelope. Additionally, the 6-week, 3- and 6-month outcome questionnaires will include the Exercise Adherence Rating Scale [20]. Participants will receive a £20 voucher after completing all of the study questionnaires at 6 months.

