### Data management

Data will be collected using a mix of paper and electronic methods. Where possible, a patient ID number will be used rather than identifiable information. Data from paper forms will be transcribed into an electronic database in Microsoft Excel stored on secure servers provided by the sponsor. Paper hard copies will be stored at the CTU and in the relevant Investigator Site Files. Study documentation will be stored securely (i.e. cupboards, shelves or filing cabinets with restricted access, e.g. within a locked office) to maintain participant confidentiality and study data integrity.

Electronic data captured at trial sites will be sent to the research team by secure NHS email. Online outcome data collection will be managed by Amplitude Clinical in ISO27001 Tier 3+ data centres approved for use by the NHS. Amplitude Clinical will not own the data — ownership is retained by the sponsor.

In order for patients to use the Squegg device, they will need to install the Squegg app on an Apple or Android smartphone/tablet. They are required to create an account within the app or log in using a Facebook or Google account. For data privacy reasons, participants will be recommended to use an email address rather than Facebook to create a user account; however, this is their own personal choice. No data will be shared between Squegg and the research team. Patients will use the device to measure grip strength and report the numerical values on the OPTimisE Follow-up Questionnaire.

Qualitative data will be organised and managed using NVivo software. Audio recordings and transcriptions will be stored on secure servers provided by the sponsor. An NHS-approved transcription service will be used that complies with data security regulations.

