**Table 3 Tab3:**
[figure not shown]
Schedule of events

*t*_0_ additional research clinic appointment *t*_1_ first physiotherapy treatment clinic appointment

Mean values and confidence intervals of the secondary outcomes (see Table 4) will be calculated if the data are normally distributed (this will be assessed using a combined test of skewness and kurtosis). If the data are not normally distributed, medians and interquartile ranges will be reported. The responsiveness of the different outcome measures will be compared, by calculating the treatment effect in the intervention group.

**Table 4 Tab4:** Outcome measures and time-points

Outcome measure	Baseline	6 weeks	3 months	6 months
Numerical rating scale of pain on gripping	X	X	X	X
Patient-rated tennis elbow evaluation (PRTEE) [15]	X	X	X	X
Tampa scale of kinesiophobia (TSK-11) [16]	X	X	X	X
Pain self-efficacy questionnaire (PSEQ) [17]	X	X	X	X
EQ 5D5L [18]	X	X	X	X
Pain-free grip strength (lbs)	OPTimisE group X	OPTimisE group X	OPTimisE group X	OPTimisE group X
	Usual care group X	Usual care group	Usual care group	Usual care group X
Maximum grip strength (lbs)	OPTimisE group X	OPTimisE group X	OPTimisE group X	OPTimisE group X
	Usual care group X	Usual care group	Usual care group	Usual care group X
Global perceived effect (GPE-11) [19]		X	X	X
Exercise adherence rating scale (EARS) [20]		X	X	X

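### The primary 6-month completion rate is counted per outcome measure, but its stated interval is the one for 50 participants, and the pooled rate does not show how many participants have usable 6-month data

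*Protocol article*

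**What the plan says.** The Outcomes section makes the 6-month outcome measure completion rate one of four primary feasibility outcomes. Statistical methods defines it as "measured as a percentage of outcome measures completed across both the intervention and usual care groups", so numerator and denominator are both counts of measures.

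The precision statement in the same section is based on 50 participants and gives "outcome measure completion rate of 70% with a 95% confidence interval of (57%, 83"%). The Sample size section sets the ceiling: "The pilot and feasibility RCT will recruit up to 50 participants or for a maximum of 12 months across three sites".

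Table 4, headed "Outcome measures and time-points", marks nine measures at 6 months in both arms. Seven are questionnaire scales (pain on gripping, PRTEE, TSK-11, PSEQ, EQ-5D-5L, GPE-11, EARS) and two are grip strength (pain-free and maximum).

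On grip, Data collection methods says "The physical measures of maximum grip strength and pain-free grip strength will also be reported by patients using the OPTimisE Follow-up Questionnaire". Data management says that to use the device "they will need to install the Squegg app on an Apple or Android smartphone/tablet". The questionnaire itself may be completed on paper, and the usual-care arm first receives the device at 6 months. The list of secondary outcomes has a separate entry for completion of the physical measures.

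Each primary outcome is rated red, amber or green against Table 2. A single red means that a main trial is not considered feasible.

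**The concern.** The precision statement counts people and the definition counts measures. An interval belongs to a defined quantity, so one of the two has to change.

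The larger issue is what the pooled rate can tell the progression decision. The Discussion explains that 6 months was chosen in order to be confident that longer-term follow-up is feasible. That is a question about participants: how many of those randomised will supply a usable 6-month outcome? A percentage of measures does not answer it.

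No other primary outcome answers it either. The follow-up rate is visits made over visits possible, in the intervention arm only, whereas 6-month outcomes arrive by post or online from both arms. The CONSORT flow diagram will show losses, but it does not enter the red/amber/green rating.

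It is also unclear whether the grip measures belong in the denominator. Two analysts could follow the text in good faith and compute different rates from the same data.

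**Working it through.** **Inputs.** Participants n = 50 and p = 0.70 with interval (57%, 83%) come from Statistical methods. Measures due at 6 months, m = 9 (7 without grip), come from Table 4. The within-patient correlation of completion (ICC) is not in the document and is taken over its range from 0 to 1. Grip completion is not in the document either, so all grip rates below are assumed.

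**Step 1: reproduce the stated interval.** The half-width is 1.96 × √(0.7 × 0.3 / 50) = 0.127, which gives 57.3% to 82.7% and rounds to the stated figures. Wilson (56.2% to 80.9%) and exact (55.4% to 82.1%) intervals for 35/50 do not match. The plan therefore used the Wald interval for 50 independent people.

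**Step 2: the interval for the quantity as defined.** The denominator is up to 50 × 9 = 450 measures, clustered within 50 people. With a common rate and a common ICC, the effective sample size is 450 / (1 + 8 × ICC).

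| ICC (assumed) | Effective n | 95% interval | Half-width (points) |
|---|---|---|---|
| 0 | 450 | 65.8% to 74.2% | 4.2 |
| 0.5 | 90 | 60.5% to 79.5% | 9.5 |
| 0.9 | 54.9 | 57.9% to 82.1% | 12.1 |
| 1 | 50 | 57.3% to 82.7% | 12.7 |

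With m = 7 the results are almost the same: 60.4% to 79.6% at ICC 0.5, and 57.9% to 82.1% at ICC 0.9. The stated interval is reached only at ICC 1, where completion is all-or-none. For any lower non-negative ICC it is wider than needed.

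**Step 3: what a pooled 70% can mean.** It is 0.70 × 450 = 315 completed measures. Two patterns give exactly that:

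- 35 people complete all nine and 15 complete none: 35 × 9 = 315.
- 35 people complete six and 15 complete seven: 35 × 6 + 15 × 7 = 210 + 105 = 315. Everyone responds and nobody completes the set.

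The pooled rate can also hide a poorly completed scale (illustrative rates). With nine measures, eight at 75% and one at 30% give (8 × 75 + 30) / 9 = 70%. With seven, six at 75% and one at 40% give (6 × 75 + 40) / 7 = 70%. This part does not depend on grip.

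**Step 4: the effect of grip, if it counts.** Let q be completion of the seven questionnaire scales and g completion of the two grip measures. The pooled rate is (7q + 2g) / 9. With q = 70%:

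- all responders do grip (g = 70%): 70%
- half of them do (g = 35%): (490 + 70) / 9 = 62.2%
- none do (g = 0): 490 / 9 = 54.4%

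Conversely, if grip completion is no higher than questionnaire completion, a pooled 70% fits questionnaire completion from 70% (g = q) to 90% (g = 0, since 7 × 90 / 9 = 70).

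**The case against.** The strongest reply is that this is a wording gap with little consequence. All follow-up measures come in one questionnaire, so nearly all-or-none completion is plausible, and at a correlation of 0.9 the half-width is 12 points rather than 13. The 4-point figure would need measures in the same booklet to be completed independently, which is unrealistic. The progression rule as described does not use the interval. All of this stands. A reader might infer from the mismatch that the plan overstates its precision, but the documents do not support that: for any non-negative correlation the stated interval errs on the wide side.

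A second reply concerns grip. A reader might infer that the grip measures are certainly in the primary rate and so are counted twice. The text does not establish this. Table 4 and the questionnaire route point towards inclusion. The separate secondary outcome for the physical measures points away from it, and so does the companion completion rate at 6 weeks and 3 months, when the usual-care arm has no grip measure due. If grip is excluded, the distortion in Step 4 disappears. What remains is an ambiguity in a quantity that is rated for progression.

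Third, the pilot has not chosen a main-trial primary outcome and plans to compare the responsiveness of its measures, so completion across the set is a legitimate interest. That supports reporting completion measure by measure. It does not support one pooled percentage, which shows neither completion of each measure nor retention of participants.

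Finally, the CONSORT diagram will give losses and numbers analysed by group. That helps a reader of the results, but the rating is not based on it.

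**Conclusion.** The point holds in a limited form. The definition counts measures and the interval counts participants. The two agree only if completion is all-or-none within a participant; otherwise the interval is somewhat too wide (half-width 9.5 to 12 points at assumed correlations of 0.5 to 0.9, against 13 stated). That alone would be minor.

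The reason to change the definition is that a pooled 70% does not identify the share of randomised participants with usable 6-month data, and no other primary outcome supplies it. This holds whether or not grip is counted. If grip is counted, the rate can also fall below questionnaire completion, for example from 70% to 62%, but that figure rests on an assumed grip rate.

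A reader might conclude that the stop/go decision would come out wrong. That cannot be shown: the Table 2 thresholds are not visible in the text at hand, and no document gives a grip completion rate. The change is worth making because the rate feeds the progression rule and the counting unit should be settled before data are seen.

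**What to change.** Define the primary rate as the proportion of all randomised participants, both arms together, who return a scoreable 6-month follow-up questionnaire, judged on the PRTEE or another patient-reported measure named in advance. The stated 57% to 83% at 50 participants then applies unchanged. Naming a measure for this purpose need not commit the main trial to it as primary outcome.

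State that grip completion is assessed only under its own secondary outcome. Tabulate completion of each other measure by arm as supporting data.

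The cost is a reworded definition and no new data collection. The small downside is that one headline rate becomes a rate plus a short table.

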### Objectives

To report the protocol for a multicentre pilot and feasibility RCT, aimed at examining the feasibility of our optimised physiotherapy treatment package and piloting trial processes for a future fully powered RCT to test clinical and cost-effectiveness compared with usual physiotherapy treatment.

Specific objectives are as follows:Estimate participant recruitment, outcome measure completion and follow-up rates in a pilot RCT.Assess patient and clinician fidelity to the optimised intervention.Explore the acceptability of the optimised physiotherapy treatment programme from both the perspective of patients and physiotherapists.

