### Outcomes

The primary outcomes for this pilot and feasibility study are as follows (see Table 2):Consent rateIntervention fidelity in the intervention groupFollow-up rate in the intervention groupOutcome measure completion rate at 6 months

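### The rule that declares a main trial feasible takes no account of recruitment pace, although estimating recruitment is the first objective

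*Protocol article*

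**What the plan says.** - **Objectives.** The first of the three specific objectives is: "Estimate participant recruitment, outcome measure completion and follow-up rates in a pilot RCT".
- **Sample size.** "The pilot and feasibility RCT will recruit up to 50 participants or for a maximum of 12 months across three sites". No minimum number is given. On where the limits come from, the article says: "These limits were a condition stipulated by the funder".
- **Outcomes.** Four primary outcomes are named and referred to Table 2: consent rate, intervention fidelity, follow-up rate in the intervention group, and 6-month outcome completion. The secondary outcomes contain no measure of recruitment per month or per site.
- **Statistical methods.** The same four outcomes are defined. The denominator of the consent rate is the eligible patients who were approached. The decision rule follows directly: a single red rating rules a main trial out. Amber without red means a main trial may be feasible with changes. For the best case: "If all outcomes are rated green (proceed), then a main trial is feasible".
- **Statistical methods, CONSORT paragraph.** A flow diagram will give the numbers assessed, eligible, consented and randomised.

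**The concern.** Recruitment has two parts: how many eligible patients appear and are approached, and what share of them agree. The consent rate measures only the second. The first depends on referral volume and on the yield of the GP database search. It decides how many sites and months a main trial needs.

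The pilot may stop on time instead of number, so it will produce direct evidence on that first part. The rule does not use this evidence, and its favourable conclusion is unconditional. The feasibility statement could therefore be wrong on the quantity that the first objective sets out to estimate, with nothing in the stated rule to prevent it.

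**Working it through.** **Inputs.** From the article: up to 50 participants, at most 12 months, three sites (Sample size); an illustrative consent rate of 25% with 95% interval 19% to 31% (Statistical methods). Assumed: totals of 10, 20 and 30 recruits at month 12, and all three sites open throughout.

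**Step 1: reproduce the article's interval.** The formula is p ± 1.96 × √(p(1 − p)/n). The article does not state n. If 50 consents are 25% of those approached, n = 50/0.25 = 200.

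√(0.25 × 0.75/200) = 0.0306, and 1.96 × 0.0306 = 0.060. The interval is 19.0% to 31.0%, as stated. So the planned precision assumes that about 200 eligible patients are approached.

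**Step 2: hold consent at 25% and vary patient flow.** Pace = recruits/(3 × 12).

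| Recruits by month 12 | Approached | Consent rate | 95% interval | Pace per site-month |
|---|---|---|---|---|
| 50 | 200 | 25% | 19.0% to 31.0% | 1.39 |
| 30 | 120 | 25% | 17.3% to 32.7% | 0.83 |
| 20 | 80 | 25% | 15.5% to 34.5% | 0.56 |
| 10 | 40 | 25% | 11.6% to 38.4% | 0.28 |

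Pace falls fivefold from the first row to the last, and the point estimate of consent does not move. Only the interval widens, and the rule as described in the text makes no use of the interval.

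**Step 3: look at the other three outcomes.** Fidelity is a share of intervention patients, follow-up a share of possible visits, and completion a share of outcome measures. None has a unit of time or site, so none falls merely because few patients were recruited.

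**Step 4: allow for a wider denominator.** The Recruitment section places confirmation of eligibility and the invitation to take part at the assessment visit. If patients count as approached only from then, non-response to mailed information or to the telephone call never reaches the consent rate. If they count from the first mailing, non-response lowers the rate, but a shortage of referred or coded patients still does not.

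**Step 5: what pace means for a main trial (illustration only).** The article gives no main-trial size. Assume 300 to 400 participants.

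- At 15 sites and 50/36 per site-month: 300/(15 × 50/36) = 14.4 months and 400/(15 × 50/36) = 19.2 months.
- At 15 sites and 10/36 per site-month: 72 and 96 months.
- To finish in 24 months instead: 300/(24 × 50/36) = 9 sites and 400/(24 × 50/36) = 12 sites at the faster pace, against 45 and 60 at the slower.

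**The case against.** **The objective is already covered.** The article turns its aim into estimates of consent, fidelity, follow-up and completion, so consent may be the intended recruitment measure, and not everything estimated need be a stop/go criterion. That is fair, and it means the article does not contradict itself. It does not repair the rule, which draws an unconditional conclusion from outcomes that cannot register patient flow.

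**The counts will be reported.** A reader might infer that the evidence on recruitment is lost. It is not: the CONSORT diagram, read with the 12-month limit and three sites, would show a shortfall. But those counts have no role in the decision.

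**Table 2 cannot be read.** This stands as a limit. The 25% is an example used to show precision and not a visible threshold, so one cannot say that this or any other consent rate would be green. The point does not depend on it, because Outcomes and Statistical methods both name the rated outcomes and pace is not among them.

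**The funder set the limits.** This also stands, and it matters for the remedy: 50 in 12 months is a cap, so 1.39 per site-month is not a target that the trial has undertaken to meet. It does not explain why pace is outside the rule.

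**Slow sites can be offset by more sites.** This is correct, and Step 5 shows it. Slow pace alone does not make a main trial infeasible.

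**This is a condensed article.** A fuller protocol may hold recruitment targets. The rule, however, is given here complete and in absolute terms.

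**Conclusion.** The concern holds as a gap in the stated decision rule. Recruitment pace can fall from 1.39 to 0.28 per site-month with the consent point estimate unchanged at 25%, and an all-green rating would still yield the conclusion that a main trial is feasible. The 1.39 follows from the article's own limits. The slower cases and the main-trial sizes are assumptions, and the structural point needs none of them.

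Two stronger readings are not supported. A reader might infer that a slow pilot would be rated green throughout; the thresholds are not visible, so the most that can be said is that slow accrual would not by itself prevent it. A reader might also infer that slow accrual proves a main trial impossible; more sites or a longer period could compensate. The change is worth making because it is cheap and affects the pilot's headline conclusion.

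**What to change.** - Report participants randomised per site per open month, overall and by identification route (physiotherapy referral screening and GP database search).
- Make the all-green conclusion under Statistical methods conditional on adequate pace, either as a fifth rated outcome in Table 2 or as an added clause in the rule.
- Derive the limits from the rate that a main trial of the expected size, number of sites and duration would need, and state those assumptions. Do not anchor them to the funder's cap of 50 in 12 months.
- Fix the limits before anyone reviews accrual data; limits set late in recruitment would follow sight of the result.
- Rate slow pace that more sites could offset as amber and not red.

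The cost is one more calculation, which needs randomisation dates and site-opening dates (the article does not say whether the latter are recorded), and a pilot that is slightly harder to rate all green.
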